### 1010 7.3.1 Secondary effectiveness analyses of continuous outcomes

1011 Secondary outcome variables that are continuous (i.e. DBP, mobility, physical activity and  
1012 quality of life) will be analyzed using the same mixed effects modeling approach used for the  
1013 primary outcome of change in SBP because all of the variables are measured at both baseline  
1014 and one-year follow-up. The three secondary variables of mobility, physical activity and quality  
1015 of life have lower bounds of 0 and are anticipated to be right-skewed, so that analysis of those  
1016 variables may not satisfy assumptions of the mixed effects modeling approach. Fortunately,  
1017 because we plan to model changes in these variables, we anticipate that assumptions on  
1018 normality of model residuals will be satisfied. Nevertheless, it is possible that after careful  
1019 evaluation of those assumptions, they are not adequately satisfied. In that case, we will use  
1020 bootstrapping to obtain valid confidence intervals for intervention effect estimates. Alternative  
1021 strategies will be either log-transforming the outcome variable or, for the Timed Up and Go test,  
1022 adopting a time-to-event analysis using, for example, Cox proportional hazards models which  
1023 would also enable us to better accommodate the censored times for individuals who could not  
1024 complete the test.

1025

### 1026 7.3.2 Secondary effectiveness analyses of binary outcomes

1027 Medication use, adherence, and physical activity levels are pre-specified binary outcomes. We  
1028 will analyze these variables using the generalized estimating equations (GEE) approach to  
1029 obtain population-averaged intervention effects. As with the primary analysis approach, strata  
1030 will be included as fixed effects in the model. In contrast to using random intercepts in the linear  
1031 mixed models used for the primary and continuous secondary outcomes, a working correlation  
1032 matrix will be used to account for clustering. More specifically, the modified Poisson GEE  
1033 approach (with log-link) will be used to obtain probability ratios (often referred to as risk ratios).  
1034 Although we expect to see correlation of outcomes within clusters, an independent working  
1035 correlation matrix will be used rather than exchangeable as it may provide greater stability with  
1036 the anticipated variability in cluster size. Robust standard errors will be used to account for  
1037 potential model misspecification. Importantly, because adherence can only be measured in

those who are taking medications, it will be important to determine the validity of a between-arm comparison. To this end, we will compare the predictors of medication use in each arm, for each of the three medications, thereby evaluating whether there is good internal validity of the comparison. In the case that we identify differences between arms in characteristics of those taking medications, we will adjust for such characteristics in the regression model.

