### 5.3 Sample size

Based on a sample of 1,250 prevalent stroke patients in 50 villages (with 25 villages per arm and on average 25 patients per village), assuming loss of 2 clusters (villages) per arm and loss of 1 patient per village on average, an intra-cluster correlation coefficient (ICC) of 0.04 (a conservative assumption), and a standard deviation (SD) for SBP pre-post change of 20 mmHg, the study has 83% power (with 2-sided alpha = 0.05) to detect a 5 mmHg net difference in pre-post change of SBP between intervention and usual care arms. Previous studies have been demonstrated that a 5mmHg difference is a meaningful change for stroke recurrence in 3-5 years. The effect size of a 5mmHg difference corresponds to a standardized effect size of 0.25 (5/20) and therefore we will have more than 80% power to detect such standardized effect sizes for secondary outcomes of interest, assuming the same level of clustering of those outcomes.

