## 7.2 Primary effectiveness analysis

The mixed effects framework will be used to model the primary outcome of short-term and long-term change in SBP with a random intercept for cluster (to account for the cluster randomized design) and fixed effects for township (to account for the stratified randomization procedure). More specifically, the primary outcome will be regressed on an indicator for treatment arm, baseline SBP, gender and age—in order to gain power—and indicator variables for township. Restricted maximum likelihood will be used together with the between–within method to calculate test degrees of freedom. Both methods have demonstrated good performance for binary outcomes and this good performance is expected for continuous outcomes, particularly when there are fewer than 40 clusters. For completeness, between-arm differences will also be presented based on the same model but with no adjustment for age and gender.

Baseline characteristics will be cross tabulated according to the randomized arm to visually check for appropriate balance and to provide an overview of the study population. If substantial baseline imbalance between the two arms is identified and the relevant variable is beyond the list of pre-specified variables for adjustment, additional sensitivity analyses adjusted for these imbalanced variables will be performed to ensure the robustness of the analysis.

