### 7.3.2 Exploratory effectiveness analyses

The exploratory outcomes of mortality, disability, stroke-related hospitalization, and stroke recurrence are binary variables. The modified Poisson GEE approach (with log-link) will be used to obtain risk ratios for binary outcomes, as described above.

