For binary outcomes, generalized estimating equations approach will be adopted to obtain population-average treatment effect and similar adjustment on township, age, sex, and baseline outcome was made. We will use a Poisson model with log link and robust standard errors to obtain risk ratios and with identity link to obtain risk differences. If models did not converge, we will use a marginal standardization approach by fitting a binomial model with a logit link to obtain risk differences and risk ratios.

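### Section 7.3.2 prespecifies township as the only covariate for the 12-month binary outcomes, leaving unused the baseline, age and gender adjustment that the primary model and Part B both make

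*Combined protocol and SAP*

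**What the plan says.** - **Primary model (7.2).** SBP is "regressed on an indicator for treatment arm, baseline SBP, gender and age", with township indicators. The stated reason for the patient-level covariates is power. A second version of the model drops age and gender but keeps baseline SBP. Section 7.3.1 applies the same modelling approach to the continuous secondary outcomes.
- **Binary secondary outcomes (7.3.2, Secondary).** The GEE is meant to "obtain population-averaged intervention effects. As with the primary analysis approach, strata" enter as fixed effects. Nothing else is prespecified. For adherence only, characteristics of medication takers that turn out to differ between arms will be added.
- **Exploratory outcomes (7.3.2, Exploratory).** "The modified Poisson GEE approach (with log-link) will be used" here too, by reference to the preceding section.
- **Missing data (7.5).** Baseline covariates found to predict loss to follow-up will be added to the regression models.
- **Part B, 3.4.1.** Analyses other than mortality are said to remain consistent with the one-year plan. For the binary GEE, "similar adjustment on township, age, sex, and baseline outcome was made".
- **Sample size (5.3).** "the study has 83% power (with 2-sided alpha = 0.05) to detect a 5 mmHg net difference", and at the matching standardised effect of 0.25, "we will have more than 80% power to detect such standardized effect sizes for secondary outcomes of interest".

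**The concern.** The binary section takes one element of the primary covariate set, the strata, and leaves out the patient-level covariates. An analyst following the text would fit arm plus township. Yet Appendix A-3, used at both baseline and follow-up, already collects medication use, the activity items behind the HEPA class, Timed Up and Go and the modified Rankin scale.

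Two things are at stake. The first is precision: current medication use is likely to depend on earlier use, and without the baseline value that variation, with any chance imbalance between 25 and 25 villages, stays in the estimate. The second is consistency: read literally, Part A and Part B give different covariate sets for the same outcomes, although Part B describes the two as consistent.

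**Working it through.** **Inputs from section 5.3.** Enrolment is 50 villages, 25 in each arm, averaging 25 patients. Attrition is then allowed for by "assuming loss of 2 clusters (villages) per arm and loss of 1 patient per village on average". That leaves 23 villages per arm and 24 patients per village. ICC is 0.04, the standardised effect 5/20 = 0.25, and alpha two-sided 0.05.

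**Input not in the documents.** The baseline-to-follow-up correlation is assumed: r_w for patients within a village, r_b for village means.

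**Formula.** On the standardised scale,

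Var = (2/23) × [0.04 × (1 − r_b²) + 0.96 × (1 − r_w²)/24],

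with power from the noncentral t on 46 − 2 = 44 df and noncentrality 0.25/√Var.

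**Reproducing the plan (no adjustment).** Var = (2/23) × (0.04 + 0.04) = 0.00696, SE = 0.0834, noncentrality = 3.00, power = 83.4%. This matches the stated 83%.

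**Adding the baseline value.** The lower figure lets baseline explain only within-village variance (r_b = 0). The upper figure uses the same correlation at both levels (r_b = r_w).

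| Assumed correlation | Power, within-village only | Power, both levels | Gain (points) |
|---|---|---|---|
| 0.2 | 84.2% | 84.9% | 0.7 to 1.5 |
| 0.3 | 85.1% | 86.7% | 1.6 to 3.3 |
| 0.4 | 86.3% | 89.2% | 2.9 to 5.8 |
| 0.5 | 88.0% | 92.3% | 4.5 to 8.9 |
| 0.6 | 89.9% | 95.6% | 6.5 to 12.1 |
| 0.7 | 92.1% | 98.4% | 8.7 to 15.0 |

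For example, at 0.5 on both levels Var = 0.00696 × 0.75 = 0.00522, SE = 0.0722 and noncentrality = 3.46. If village means were more strongly correlated than patients (r_w = 0.5, r_b = 0.8), the gain would be 14.1 points.

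**Check on the model actually planned.** The modified Poisson GEE (independence working correlation, robust SE) was simulated with 46 villages of 24. Event rates are assumed, since the documents give none.

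- At 50% vs 62.5% and a binary correlation of 0.50, power went from 84.4% to 89.2% with village effects correlated 0.3 over time, and from 84.8% to 96.2% with them correlated 0.71. The mean log risk ratio was 0.223-0.225 with and without baseline.
- With township in the model and control-arm risks of 30%, 50% and 65%, gains were 1.6-1.9 points at a binary correlation near 0.19, 4.4-5.2 near 0.32, 6.0-7.5 near 0.40 and 9.5-11.4 near 0.48. Village effects were given a stronger correlation than the binary outcomes, which is why these lie at or somewhat above the table's upper column.

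The gain from age and gender was not computed; the documents give no input for it.

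**The case against.** **Silence is not exclusion.** Section 7.3.2 does not rule covariates out. Part B's claim of consistency could mean that the team always intended the fuller set, and Part B cites a published SAP that is not in this file. That stands in part: a reader might infer that the 12-month and long-term risk ratios will certainly come from different models, and the text does not establish this. It does establish that the covariates are not prespecified in Part A. The conditional adjustments in 7.3.2 and 7.5 do not fill the gap, because they depend on what the data show and do not name the baseline outcome.

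**No harm to validity.** This stands. A reader might infer bias or an underpowered comparison; neither is supported. The township-adjusted risk ratio with robust errors is valid under randomisation. The claim in 5.3 does not rely on covariates and already allows for losing four villages (46 × 24 = 1,104 analysed); Part B reports 1,266 completers at 12 months. With 25 villages of 25 per arm, the same formula gives 87.1% unadjusted. Section 7.1.2 specifies a significance test only for the primary outcome, so wider intervals are the practical cost.

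**No fixed number of points.** This also stands. Any single figure for lost power rests on a correlation the documents do not report.

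**Not every binary outcome qualifies.** Mortality, recurrence and stroke hospitalisation are follow-up events. Baseline adherence is undefined for patients not taking the drug then, so adjusting for it would drop new users.

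**Conclusion.** The point holds as a free improvement in precision and a passage to reconcile, not as an error in the analysis. The binary GEE names township as its only prespecified covariate, while 7.2 and Part B 3.4.1 both name baseline outcome, age and sex. From 83.4% power at the plan's inputs, adding the baseline value would give about 88-92% if the correlation is 0.5. The range is about +1 to +3 points at 0.2-0.3 and +9 to +15 at 0.7. These figures assume the 5.3 inputs carry over to binary outcomes and, for the upper ends, equal correlation at village and patient level. The gain applies to medication use, HEPA class, Timed Up and Go at 14 s and the modified Rankin category.

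**What to change.** In 7.3.2, list the covariates by outcome:

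- **Medication use (each drug), HEPA class, Timed Up and Go at 14 s, modified Rankin category:** township, age, gender and the baseline value of the same outcome. Table 4 leaves open how Timed Up and Go non-completers are handled; apply the same rule at baseline as at follow-up.
- **Mortality, recurrence, stroke hospitalisation and adherence:** township, age and gender only.
- **Supportive analysis:** mirror 7.2 by dropping age and gender while keeping the baseline value.
- **Non-convergence:** use the marginal standardisation fallback already written in Part B 3.4.1.

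This also makes Part B's statement of consistency true of the Part A text for the outcomes with a baseline value. The cost is a few sentences of SAP wording plus the Timed Up and Go rule; no new data are needed. Because arm is independent of baseline by randomisation, the arm coefficient in a main-effects log-link Poisson model still estimates the population-averaged risk ratio, so the target does not change.

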### 5.6 Data collection

We will invite participants in both the intervention and control arms to visit the village clinics to receive a comprehensive survey and standard anthropometric measures at baseline and the end of the study (12 months). The data collection will be conducted following a standard protocol by trained staff recruited from the Center of Disease Control and Prevention (CDC) of a nearby county, who are completely blinded of randomized allocation of villages and will not be involved in the implementation of the intervention. For patients, a brief interviewer-administered questionnaire (**Appendix A-3**) will be completed using Qualtrics, an online-survey platform, which is able to ensure the quality of data through setting the format and force response. The questionnaire will collect data on demographic information, disease history, medication use and adherence, lifestyle behaviors, and utilization of healthcare services including hospitalization. Patients will have a physical examination comprising of assessment of blood pressure, weight, height, waist circumference and the "Timed Up and Go" test.

Village doctors will be invited to complete a self-administered knowledge-attitude-practices questionnaire (**Appendix A-4**) including questions regarding their demographic characteristics and clinical practice experience. The survey consists of 6 questions regarding their knowledge on the secondary prevention of stroke guidelines and 17 questions regarding their attitude and practice in delivering the stroke secondary prevention to patients evaluated by using 5-Likert scale.

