## 5.7 Outcome evaluation

The primary outcome is systolic blood pressure (SBP) of participants. The effectiveness of the program will be evaluated by the SBP at 1-year follow-up between the intervention and the control arm. Blood pressure is measured on the right upper arm (or left arm if the right arm is disabled) with participant seated after 5 minutes of rest using an electronic blood pressure monitor (Omron HEM-7052). Two measurements are taken, and the mean value is calculated. If the differences between the 2 SBP is larger than 10 mmHg, a third measurement is conducted, and the mean value of the only or the last 2 reading is calculated.

Secondary outcomes include participants' diastolic blood pressure, mobility, medication adherence, physical activity level and quality of life. Mobility is measured using the Timed Up and Go test, a simple and quick functional mobility test that requires the participants to stand up, walk 3 meters, turn, walk back, and sit down. Medication adherence is measured using the 4item Morisky Green Levine Scale with scores ranging from 0 to 4 with a higher score indicating lower medication adherence. Participants will respond to the 4 questions with yes or no for each type of medicines (antihypertension, aspirin and statin) if they were prescribed by the physicians before. Physical activity level is measured using the short version of the International Physical Activity Questionnaire (IPAQ). Participants were asked to recall the frequency and duration of rigorous activities, moderate activities and walking they performed in the past 7 days. Quality of life is measured using EuroQoL- 5 Dimensions-5L (EQ5D).

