| Quality of life      | 
Quality of life is measured with EuroQol-5 Dimensions-5L (EQ5D), which consist of five dimensions and each with five levels of perceived problems. These dimensions are combined to give a five-digit code and a single index-based numerical value (ranged from 0 to 1) will be derived based on the value set for Chinese population.
                                                                                                                                                                                                                                                                                                                                                                                                                                                | Continuous as utility                                                                                  |
| Medication use       | 
Medication use is self-reported for each of three distinct medication types: anti-hypertensive medicine, aspirin and statin.
                                                                                                                                                                                                                                                                                                                                                                                                                                                                                                                                                                                                                                                           | Binary yes/no for each of three medication types.                                                      |

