| Medication adherence | 
Self-reported medical adherence is measured by Morisky Green Levine Scale separately for anti-hypertensive medicine, aspirin and statins if the participant was taking the medicine. A score ranged from 0 to 4 are calculated by summing all coded answers where lower scores correspond to better medication adherence.
                                                                                                                                                                                                                                                                                                                                                                                                                                                              | The variable will be dichotomized as high adherence (0) vs. low to medium adherence (1-4).             |

---

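### Medication adherence is compared only among people taking each drug at follow-up, a group the intervention may change, and adjusting for measured differences may not restore a randomised comparison

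*Combined protocol and SAP*

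**What the plan says.** Table 4 of Part A makes adherence a secondary outcome for antihypertensives, aspirin and statins separately. It is split at score 0 against 1 to 4, and scored only "if the participant was taking the medicine". Outcomes are assessed at baseline and 12 months (section 5.6), so taking the drug at the outcome visit is a post-randomisation condition.

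Section 7.3.2, on binary outcomes, uses a modified Poisson GEE with log link to obtain risk ratios. Because adherence can be measured only in "those who are taking medications, it will be important to determine the validity of a between-arm comparison", it plans a check: "we will compare the predictors of medication use in each arm, for each" of the three drugs. The remedy follows if the check identifies "differences between arms in characteristics of those taking medications, we will adjust for such characteristics in the regression model". The section does not list candidate characteristics, say what size of difference triggers adjustment, or limit adjustment to baseline values. It plans no adherence analysis in all participants and none for unmeasured selection.

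Medication use is a separate secondary outcome in the same table: "Medication use is self-reported for each of three distinct medication types". Section 5.7 gives a different denominator for adherence, asking the questions about each drug "if they were prescribed by the physicians before".

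**The concern.** Randomisation balances the arms among everyone enrolled. It does not balance them among people who happen to be taking a drug a year later if the intervention influences who that is. Such influence is plausible here. Village doctors are trained on guidelines and essential medications (section 5.5.1), and their monthly visit record allows the prescription to be changed (Appendix A-2). Use is tested as an effectiveness outcome.

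People who start a drug because of the intervention, and people who stop it in the control arm, may differ from steady users in ways the survey does not capture. Someone who stops altogether leaves the denominator instead of counting as non-adherent. Three secondary risk ratios are therefore open to selection bias in either direction. The issue carries into Part B, which keeps adherence as a secondary outcome (section 3.3.2) and follows the one-year plan for binary outcomes (section 3.4.1). There, differential survival adds to it.

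**Working it through.** **The plan's own figure.** The documents give no number specific to adherence. The nearest is the 83% power in section 5.3. Design effect = 1 + (24 − 1) × 0.04 = 1.92. Effective n per arm = 23 × 24 / 1.92 = 287.5. For 5 mmHg with SD 20, a t-based calculation with 44 degrees of freedom gives 83.4%, which reproduces the figure. The normal approximation gives 85.0%.

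**Step 1: users-only ratio when adherence is truly unaffected.** All inputs are assumptions. Control use is set at 46.2%, borrowed from the registry figure for continued use in the Background, since the documents give no use rate for this population. People who would take the drug in either arm adhere at 60% in both arms. Those who take it only because of the intervention adhere at rate a.

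- Users-only ratio = [(0.462 × 0.60 + (u − 0.462) × a) / u] / 0.60, where u is use in the intervention arm.
- Combined ratio (taking and score 0, all participants) = [0.462 × 0.60 + (u − 0.462) × a] / (0.462 × 0.60).
- Example, u = 0.562 and a = 0.30: (0.2772 + 0.0300) / 0.562 = 0.547, and 0.547 / 0.60 = 0.91. Combined: 0.3072 / 0.2772 = 1.11.

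| Use, intervention arm | a | Users-only | Combined |
|---|---|---|---|
| 46.2% | any | 1.00 | 1.00 |
| 56.2% | 30% | 0.91 | 1.11 |
| 56.2% | 60% | 1.00 | 1.22 |
| 56.2% | 75% | 1.04 | 1.27 |
| 66.2% | 30% | 0.85 | 1.22 |
| 66.2% | 75% | 1.08 | 1.54 |

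The same calculation with use rising from 20% to 30% gives 0.83 to 1.08 among users. From 70% to 80% it gives 0.94 to 1.03.

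**Step 2: does adjustment repair it?** One million people were simulated, without villages. A measured covariate X and an unmeasured one U both affect use and adherence, and the arm affects use only, so the true adherence ratio is 1.00. The log-odds coefficient was 0.5 for X and 0.5, 1.0 or 1.5 for U. Use rose from 46% to between 63% and 68%. Poisson log-link regression among users gave:

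- unadjusted: 0.93 to 0.96
- adjusted for X: 0.93 to 0.98
- adjusted for X and U: 0.99 to 1.00
- with the U coefficient set to zero, adjusted for X: 1.00

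With no shift in use, the ratios stayed at about 1.00 throughout.

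**Step 3: an example with a real benefit.** Assume 60% use in control, with half of users highly adherent (30% of all participants). Assume 75% use under intervention: the 60% who would use anyway adhere at 55%, the extra 15% at 30%. Then 0.60 × 0.55 + 0.15 × 0.30 = 0.375. The users-only ratio is (0.375 / 0.75) / 0.50 = 1.00, although adherence among those who would use anyway improved by 0.55 / 0.50 = 1.10. The combined ratio is 0.375 / 0.30 = 1.25. Medication use alone also shows 0.75 / 0.60 = 1.25, so in this example the plan already reports a gain of that size.

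**Step 4: precision in a subset.** Section 5.3 claims more than 80% power for a standardised effect of 0.25 in secondary outcomes, with 24 patients analysed per village. If 46.2% contribute, there are about 11.1 per village, the design effect is 1 + 10.1 × 0.04 = 1.40, and effective n is 23 × 11.1 / 1.40, about 182 per arm. Power is then about 66% by the normal approximation, against 85.0% for the full sample on the same basis. It is 41% with 20% users and 81% with 80%.

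**The case against.** The SAP did not overlook this. It questions the validity of the comparison itself and specifies a check for each drug, so the dispute is only whether the remedy is strong enough. That stands.

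A reader might infer that the intervention certainly changes who takes each drug, or that adjustment can never work. The documents support neither. The aim stated in section 5.5 is adherence and physical activity. A change in use is a reasonable expectation, not a documented fact, and without a change in its level or composition there is no bias. Adjustment does recover the truth if all common causes are measured. The SAP does not claim that, and comparing measured predictors cannot show it.

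A reader might also infer that a successful intervention would go unseen. Step 3 shows why that goes too far: the planned medication-use outcome would show the gain in uptake.

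Replacing the users-only outcome with the combined one would bring its own problem. In Step 1 the combined ratio reaches 1.54 with no change in adherence among those who would take the drug anyway, because it largely reflects uptake. It also counts people never prescribed a drug as non-adherent, and section 5.2.3 admits haemorrhagic as well as ischaemic stroke. This objection stands, so the combined outcome belongs beside the planned analysis.

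Finally, sections 5.7 and Table 4 can be read as nested: who is asked, then who is scored. That reading is possible but is not stated, and a person prescribed a drug who has stopped falls in one set and outside the other.

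**Conclusion.** The concern holds as a limit on what the users-only comparison can show. Followed as written, the plan can yield a biased risk ratio for each of the three drugs, and its check cannot exclude that. In the scenarios examined, a true ratio of 1.00 appears as anything from 0.83 to 1.08. With an unmeasured cause and the larger shift in use, 0.93 to 0.98 remains after adjustment. These values rest on assumed use, adherence and confounding strengths. The bias is nil if use does not shift, and its sign depends on whether people drawn into treatment adhere less or more than the rest. Adherence is secondary, and section 7.1.2 ties the significance test to the primary outcome, so the blood pressure conclusion is untouched.

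**What to change.** For each drug class, add two analyses with the same modified Poisson GEE:

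1. Taking the drug and score 0, against not taking or score 1 to 4, in all participants with follow-up. Label it a combined uptake-and-adherence outcome and read it beside the medication-use result.
2. The same outcome in participants recorded at baseline as prescribed or taking that drug, so that those who stop count as non-adherent. The baseline questionnaire in Appendix A-3 asks about past-year prescription of aspirin, antihypertensives and lipid-lowering medicines; state how statins are identified within the last group.

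Keep the users-only analysis. Report it as a conditional, non-randomised comparison that does not by itself support a causal claim about adherence, and restrict adjustment in it to baseline characteristics. Use one stated denominator in section 5.7 and Table 4, and carry the wording into Part B.

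The cost is SAP text and a few more model fits, with no new data. The first analysis mixes uptake with adherence and includes people never prescribed the drug. The second has a smaller sample, with the loss of power shown in Step 4. Since Part B section 3.1 places the 12-month assessment in July 2018, additions to Part A should be dated and labelled as made after it.
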